##### What (Materials)

Each participant will have to fill in an informed consent form before any measurements. Participant consent forms are tailored to meet the General Data Protection Regulation standards and local ethical requirements in Finland, Spain, and Hungary. A total of 2 similar score sheets will be created for the physical fitness measurements, 1 for the participant and 1 for the researchers. General reference values and the interpretation of the results will be presented after the measurement session. This material will also be displayed on the webpages for the participant to view later. Participants will also fill a self-completion quality of life questionnaire (World Health Organization Quality-of-Life) before the test and UEQ at the end of the test. The security of the participants in the event will be carefully designed and considered. A security plan has been developed and will be gone through for all participating event staff members. For the assessment or measurement, simple materials will be used, including stop watches, tape measures, chairs, hand weights (3 kg and 5 kg), and cones.

Approximately 40 participants in Finland and all participants in Spain and Hungary will receive armband sensor devices (SenseWear Armband; BodyMedia Inc), which will measure their physical activity levels on a daily basis for 24 hours. During the measurement period, participants will also be keeping a diary. In Finland, other equipment will include a Jamar hand dynamometer (JWL Instruments), Tanita MC-780MA body composition analyzer, peak expiratory flow measurements (Mini Wright; Clement Clarke International), and a standout smart balance board (Smartifier Ltd). In Hungary, participants will receive information regarding the 8-week training program and related relaxation exercises. The training program uses a 1.5 km outdoor fitness trail with 19 physical exercise stations equipped with information boards, which show different variations in how to use the stations and how to get to the next station. In Spain, the Standout Balance Board and Xiaomi Miband 5 will also be used. A small group of participants will receive a smart wristband watch (Galaxy Watch 3), which measures the average daily activity performed on a 4-day basis. The training program will be based on recreational football playing.

##### What (Procedures)

The following physical fitness components will be covered in the physical fitness test in Finland and Spain: cardiorespiratory endurance, muscle strength and endurance, balance, agility, speed, flexibility, and body composition. After signing the consent form and filling the quality of life questionnaire (World Health Organization Quality-of-Life Scale), the participants will go through the following measurement points step by step in selected locations (ie, sports halls, nursing homes, fitness parks, and outdoor facilities): (1) 6-minute walk test or nonexercise cardiorespiratory fitness test, (2) handgrip strength test, (3) 30-second arm curl test, (4) 30-second chair stand test, (5) Smartifier balance board test, (6) 8-foot up-and-go test, (7) backward walk test, (8) 10 m walk test, (9) chair sit-and-reach test, (10) back scratch test, (11) height and body composition measurements, and (12) peak expiratory flow measurement. In Hungary, which is used as a control group, physical fitness will be measured by following a protocol defined in the senior fitness test manual [28]. After finishing the measurement track, participants will fill the UEQ, which also includes an open text box to propose improvement suggestions or give complaints about the testing procedure.

In Hungary and Spain, the physical fitness testing battery will be used to determine the baseline (T0, before the start of the training program intervention) and conduct the postmeasure (T1) at the end of the 8-week training program. Participants’ daily activities will also be measured with the armband device for 4 days during the training period. In addition, in Spain, some of the participants will also use a smart wristband watch (Galaxy Watch 3). In Hungary, the training program will include outdoor training on fitness trails with 19 stations in a 1.5 km route. Feedback will be collected from participants after the training intervention. In Spain, outdoor training on recreational football will be performed in a network of distributed resources and public spaces. Feedback will be collected from participants after the training intervention.

##### Who Provided

In Finland, physiotherapy students will collect the materials under the supervision of experienced physiotherapy teachers and VITALISE project team members. The testing protocol will be introduced and trained for the students on a separate occasion before the measurement events. VITALISE project team members have extensive experience in planning and implementing Living Lab research projects and protocols in health and well-being research settings. In Hungary, Trebag staff will assist in the data collection of physical fitness tests with the guidance of an experienced and qualified leader. Outdoor fitness occasions will be facilitated by qualified coaches. In Spain, the Gaia staff will assist in data collection of the physical fitness tests, together with students of science degree in physical activity and sport from Deusto University, who will also assist in the fitness occasions.

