##### How

During the measurement day in Finland and Spain, there will be an open access period when measurements will be conducted by following the walk-in principle. Participants will circulate individually from the measurement point to another, where they will receive instructions from students (physiotherapy or similar). After finishing the measurement track, participants will go to the meeting point where general reference values and the interpretation of the results can be self-read from the presented materials. At the meeting point, participants will also fill the UEQ questionnaire. In Hungary, the process will be similar; however, participants will be invited, and the measurement track will be based on a protocol defined in the senior fitness test manual [28].

The physical fitness testing protocol will be first run in Finland. Following this, modifications will be made to the testing protocol if needs for change are identified based on participant feedback. The same or revised protocol will then be used in Spain to collect cross-country data. In Hungary, a different protocol [28] will be used to get the baseline for UX and be able to compare how the extended measurement protocol influences the UX. At the end of the project, result comparisons regarding measurement day experiences will be made between the 3 countries and 2 different measurement protocols.

The participants receiving the armband device will be invited to a specific location (eg, university campus), where they will receive detailed information about the test and how to keep the activity diary. In Spain, some of the participants will also receive a Galaxy Watch 3 device, which is used for similar purposes as the armband device. In Finland, participants will keep the device for 1 day (24 hours). In Hungary and Spain, participants will keep it for 4 days (96 hours). Owing to the limited number of devices and device rotation, the measurement time will vary between participants.

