The main results will focus on understanding older adults’ physical fitness levels by defining and testing comprehensive testing patterns in a cross-country setting. Single test results with reference values exist; however, surprisingly, a wider understanding of older adults’ fitness levels is lacking. From prior studies, it is acknowledged that the vast majority of the participants recruited via open calls will be persons with good fitness and functioning levels. Therefore, older adults with lower physical fitness will be recruited from nursing homes to also cover more fragile and less fit older adults. By combining the daily physical activity level sensor measures and physical fitness test results, novel and insightful information about the physical status of the participant can be verified. The perceived UX of the proposed comprehensive physical fitness level research protocol will be compared with a well-established but less comprehensive protocol. It is expected that there will be no significant differences regarding UX; therefore, in the future, a more comprehensive protocol should be applied to reveal a better understanding of the older adults’ physical fitness levels. Furthermore, the pre- and posttraining period physical fitness levels will be compared in the cases of the Spain and Hungary case studies. These results are expected to reveal that the training program affects participants’ physical fitness level as well as provide suggestions from participants on how to improve the training program.

#### Case Study 5

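### Case study 4, Spain: the student group that helps collect the T0 and T1 fitness tests also assists in the training, and nothing keeps a student from scoring participants he or she helped train

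*Protocol article*

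**What the plan says.** **Who tests and who trains.** The protocol article, Cross-country Case Study 4, Who Provided, states for Spain: "In Spain, the Gaia staff will assist in data collection of the physical fitness tests". They do so with "students of science degree in physical activity and sport from Deusto University, who will also assist in the fitness occasions". For Hungary the same section names Trebag staff, guided by a qualified leader, for the tests, and says of the training: "Outdoor fitness occasions will be facilitated by qualified coaches".

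**Who runs the stations.** Under How, participants in Finland and Spain move from one measurement point to the next, where "they will receive instructions from students (physiotherapy or similar").

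**When the tests are done.** Under What (Procedures), for Hungary and Spain, "the physical fitness testing battery will be used to determine the baseline (T0"), and the same battery serves to "conduct the postmeasure (T1) at the end of the 8-week training program".

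**How the result is read.** Discussion, Case Study Outcomes, Case Study 4, plans a comparison of fitness before and after training in Spain and Hungary and says: "These results are expected to reveal that the training program affects" participants' fitness.

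**The concern.** Most stations in the battery depend on the participant's effort and on a person with a stopwatch, a count or a tape measure. At T0 no training has taken place. At T1 a student may be scoring people whom he or she helped through the 8-week programme, and knows that this is the post-test. Warmer encouragement, a doubtful repetition counted or a slightly earlier stop of the watch would all move the result in the direction the Discussion expects.

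In a trial with an untrained group measured by the same assessors, part of such a drift would show up in that group. Spain has none. Hungary is called a control group under What (Procedures), but its participants also train for 8 weeks and follow a different test protocol. The How section gives the reason for that difference: a baseline for user experience. A shift in scoring at T1 would therefore be read as a training effect. It cannot be repaired in the analysis afterwards.

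**Working it through.** **Step 1: does the text put both roles on the same group?** The Spanish sentence in Who Provided separates collecting the test data from the fitness occasions. The Hungarian sentence just before it uses the same term for sessions led by coaches, and When and How Much calls the test days measurement events. The students' second role is therefore the training.

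**Step 2: is there a rule that separates the roles at T1?** None appears in case study 4 (Who Provided, How, Tailoring) or in the data analysis plans for the case studies. Training and supervision of student testers are described for Finland only.

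**Step 3: which stations are exposed?** What (Materials) lists mainly hand tools, including stopwatches, tape measures and chairs. Set against the stations in What (Procedures):

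- Scored by hand: arm curl, chair stand, up-and-go, backward walk, 10 m walk, 6-minute walk (where used), sit-and-reach, back scratch.
- Read from a device and less exposed: handgrip, balance board, body composition, peak expiratory flow. Handgrip and peak flow still respond to encouragement.

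**Step 4: illustrative size.** The plan has no figure of its own to reproduce.

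Inputs:

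- n = 20 to 40, the recruitment estimate for Spain (To Whom).
- Paired t test, one of the methods listed in the data analysis plans.
- Assumed, not in the document: two-sided 5% level, no true training effect, an assessor shift d at T1 in units of the between-person SD, applied to every participant, and a T0-T1 correlation rho.

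Formulas: SD of change = √(2(1 − rho)). Non-centrality = d·√n / √(2(1 − rho)). The probability of a significant result comes from the non-central t distribution with n − 1 degrees of freedom.

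Example with d = 0.2, rho = 0.8, n = 20: SD of change = √0.4 = 0.632; non-centrality = 0.2 × 4.472 / 0.632 = 1.414; critical value 2.093; probability 0.269.

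| d | rho | n = 20 | n = 30 | n = 40 |
|---|---|---|---|---|
| 0.2 | 0.5 | 14% | 18% | 24% |
| 0.2 | 0.7 | 20% | 28% | 36% |
| 0.2 | 0.8 | 27% | 39% | 50% |
| 0.2 | 0.9 | 48% | 66% | 79% |
| 0.1 | 0.8 | 10% | 13% | 16% |
| 0.3 | 0.8 | 52% | 71% | 83% |

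Without a shift, every cell would be 5%.

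**Step 5: dropout.** The n above is recruited, not tested at T1. Hungary expects 30 to 50 recruits to fall to 20, a retention of 20/50 = 40% to 20/30 = 67%. Applied to Spain, this gives 20 × 0.40 = 8 to 40 × 0.67 = 27 pairs. At 10 and 15 pairs, with d = 0.2 and rho = 0.8, the probabilities are 15% and 21%.

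**The case against.** **The text says less than it may seem to.** A reader might infer that the students deliver the programme and then test their own trainees. The document says only that a group assists in both tasks. The How section also mentions instructors and monitors for the web-based sessions, and Gaia staff share the testing. Nothing says that each student does both jobs, or that the same students test at T0 and T1. This stands: the supportable statement is that overlap is not excluded.

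**Hungary is not a model of planned separation.** A reader might take its staffing as a deliberate safeguard. The document names different groups for testing and training, but it does not say that the coaches are kept away from T1. This stands too. Hungary's text shows different staffing and no more.

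**The pre/post change is not the main target.** Case study 4 is there chiefly to develop and test a measurement protocol and to compare user experience. The training comparison is one further item, in a small exploratory arm. This limits the weight of the point. It does not remove it, because the Discussion still expects the result to show an effect of training.

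**Other biases remain.** Retest learning, season, selective dropout and participants' expectations would stay mixed with any training effect, and assessors would still know which visit is the post-test. This is correct. The fix removes one source among several.

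**The size rests on assumptions.** Neither the shift nor the correlation comes from the document, and the calculation lets every tester apply the full shift to every participant. This is correct, and it is why the table is a range and not an estimate.

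**Such detail belongs in a site protocol.** What (Materials) for phases 1 and 3 says that each case study has its own written protocol, and scripts and rotas may well be left to it. That is fair for the detail. But the article itself gives the staffing, and the staffing as given allows the overlap.

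**Conclusion.** The point holds in a limited form. In Spain the student group that helps collect the T0 and T1 tests also assists in the training, and the document does not stop a student from scoring, at T1, participants he or she helped train. For the hand-scored stations, a difference in encouragement or leniency at T1 would be inseparable from the training effect, because there is no untrained comparison group.

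The document does not show that such bias will occur or how large it would be. Under an assumed 0.2 SD shift and no true effect, the chance of a significant paired test rises from 5% to between 14% and 79% across correlations of 0.5 to 0.9 and n of 20 to 40. If only 10 to 15 pairs reach T1, it is about 15% to 21% at a correlation of 0.8.

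This is not a failure to blind assessors to treatment allocation, since nobody in Spain is allocated to anything. It is a lack of assessor independence in an uncontrolled comparison, and it deserves a cheap correction rather than a redesign.

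**What to change.** For Spain, add to the case study 4 testing procedure:

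- At T1, the hand-scored stations (arm curl, chair stand, up-and-go, walk tests, sit-and-reach, back scratch) are scored by Gaia staff or by students who did not assist in that participant's training sessions.
- The same fixed instruction and encouragement script is used at T0 and T1.
- The researchers' T0 score sheet is out of sight of the T1 scorer.
- Where overlap cannot be avoided, it is reported as a limitation of the pre/post result.

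Students who helped train a participant can still take the questionnaires and the height and body composition measurements.

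The cost is a rota change among people already named and a few sentences in the testing procedure. It needs no extra staff, participants or visits. The downside is less flexible staffing on the T1 day. The change has to be in place before T1.

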##### How

During the measurement day in Finland and Spain, there will be an open access period when measurements will be conducted by following the walk-in principle. Participants will circulate individually from the measurement point to another, where they will receive instructions from students (physiotherapy or similar). After finishing the measurement track, participants will go to the meeting point where general reference values and the interpretation of the results can be self-read from the presented materials. At the meeting point, participants will also fill the UEQ questionnaire. In Hungary, the process will be similar; however, participants will be invited, and the measurement track will be based on a protocol defined in the senior fitness test manual [28].

The physical fitness testing protocol will be first run in Finland. Following this, modifications will be made to the testing protocol if needs for change are identified based on participant feedback. The same or revised protocol will then be used in Spain to collect cross-country data. In Hungary, a different protocol [28] will be used to get the baseline for UX and be able to compare how the extended measurement protocol influences the UX. At the end of the project, result comparisons regarding measurement day experiences will be made between the 3 countries and 2 different measurement protocols.

The participants receiving the armband device will be invited to a specific location (eg, university campus), where they will receive detailed information about the test and how to keep the activity diary. In Spain, some of the participants will also receive a Galaxy Watch 3 device, which is used for similar purposes as the armband device. In Finland, participants will keep the device for 1 day (24 hours). In Hungary and Spain, participants will keep it for 4 days (96 hours). Owing to the limited number of devices and device rotation, the measurement time will vary between participants.

In Hungary, outdoor training on fitness trails will be introduced by guided visits where participants can try to experience fitness station activities with the help of a qualified trainer. In the fitness stations, participants will perform exercises with their own body weight. At the stations, boards will show the planned, recommended tasks that participants can perform by 3 variants and how to get to the next station. Feedback collection and postmeasurement (T1) will be conducted after 8 weeks of training interventions.

In Spain, outdoor training on recreational football will be performed in a network of distributed resources and public spaces. Owing to possible COVID-19 restrictions, web-based sessions will be organized if physical restrictions are in place, following 2 methodologies if needed: through live sessions with the instructors and through tutorials so the users could watch them at any time, which will be available on the Gaia Cluster YouTube account. For group web-based exercises (where users are at their homes), WhatsApp group video calls will be used. In these calls, the monitors will bring the classes home and give instructions so that the participants can feel part of the group again. Feedback collection and postmeasurement (T1) will be conducted after 8 weeks of training interventions.

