#### Cross-country Case Study 4: Multidimensional Physical Fitness Testing Protocol for Aging Persons

##### Why

With older adults, functional independence is directly dependent on physical fitness. Aging is inevitably associated with the declining functions of systems and organs (heart, lungs, blood vessels, and skeletal muscles) that determine physical fitness. However, aging is a complex process involving many variables that interact with one another, for example, lifestyle factors, chronic diseases, and genetics. Relatively little is known about the physical fitness levels needed to maintain physical independence. Many studies have shown that measurements of physical performance can predict future mobility disability, institutionalization, and mortality. Studies have also shown a strong association between measurements of physical performance and self-reported mobility disability. However, most of these prospective studies used only a few measures of physical performance or were targeted at functionally limited persons; therefore, assessments have only limited value for counseling. Therefore, this case study will develop and test a physical fitness testing protocol for older adults in real-life settings in 3 countries: Finland, Spain, and Hungary.

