##### When and How Much

The first measurement events in each country will happen for 1 or 2 days in spring to summer of 2022 at a spacious venue (eg, sports hall, gym, or similar space having enough space to establish the measurement track). Each participant will complete the measurement track once, which will take approximately 20 to 25 minutes in Finland and Spain and 15 to 20 minutes in Hungary. In Finland, the main measurement events will take place first, and smaller measurement events in nursing homes will take place soon after the main measurement session. Participants with armband sensor devices will keep the device for 1 day. In Hungary, after the measurement event, the outdoor fitness training program will start, and it will last for 8 weeks. Participants with armband sensor devices will keep it for 4 days. In Spain, outdoor physical interventions will last for 8 weeks after the measurement event.

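### Case study 4 compares the two fitness protocols on user experience only, yet expects to recommend the longer one for the better understanding of fitness it gives

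*Protocol article*

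**What the plan says.** All references are to the protocol article, Cross-country Case Study 4, unless stated.

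- **Rationale (Why).** Earlier work is criticised because "most of these prospective studies used only a few measures of physical performance" or because it was aimed at functionally limited people.
- **Allocation (What (Procedures)).** Finland and Spain use a track of 12 measurement points. Hungary, described as a control group, follows the cited senior fitness test manual.
- **Purpose of the Hungarian protocol (How).** Hungary's protocol differs so that it can serve as the UX reference for judging the effect of the longer track on UX. The closing comparison is worded this way: "result comparisons regarding measurement day experiences will be made between the 3 countries and 2 different measurement protocols".
- **Duration (When and How Much).** The track takes "approximately 20 to 25 minutes in Finland and Spain and 15 to 20 minutes in Hungary".
- **Expected conclusion (Discussion, Case Study Outcomes, Case Study 4).** Perceived UX of the longer protocol is set against that of the shorter, established one. The stated expectation is: "It is expected that there will be no significant differences regarding UX". From this the article draws a recommendation: "therefore, in the future, a more comprehensive protocol should be applied to reveal a better understanding of the older adults’ physical fitness levels".

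**The concern.** The Discussion sentence moves from an expected finding about UX to a recommendation about measurement. If participants find both tracks equally tolerable, that removes one reason not to use the longer one. It gives no reason to use it. The reason offered is a better understanding of fitness levels, and no stated comparison bears on that.

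This is separate from how similarity of UX is judged. Even if equal UX were shown convincingly, the second premise would stay untested.

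What is at stake is the case study's main message about its testing protocol. If some added stations largely repeat what the shared ones show, they cost participant and staff time and add little. The plan as stated would not reveal this. Revision of the track after Finland is also tied only to participant feedback (How; Tailoring), so overlap between stations would not prompt a change there either.

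**Working it through.** The article states no sample size calculation, power or error rate for case study 4, so there is no figure of its own to reproduce. The check has two parts: reading the planned analyses against the conclusion, and sizing what an added-value analysis could use.

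**1. Does any stated analysis test the second premise?**

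| Stated analysis | Where | What it tests |
|---|---|---|
| Measurement-day experience, 3 countries and 2 protocols | How | UX |
| Perceived UX, longer v shorter protocol | Discussion, Case Study 4 | UX |
| Fitness before v after training, Spain and Hungary | Discussion, Case Study 4 | The training programme |
| Sensor activity combined with fitness results | Discussion, Case Study 4 | Physical status; no contrast of protocols, or of added v shared stations |
| General list of tests and correlations | Analysis, Phase 2 | No contrast specified for this question |

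None compares what the two protocols reveal. No group is planned to do both protocols as separate tracks. Protocol also coincides with country, with age range (over 67 in Finland, 60 to 80 in Spain, over 55 in Hungary) and, in part, with walk-in v invited attendance. Comparing fitness results between Hungary and the other two countries would therefore not answer the question. An analysis within extended-track participants could.

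**2. Extra time.** The ranges are 20 to 25 minutes and 15 to 20 minutes. Pairing like ends gives 20 − 15 = 5 and 25 − 20 = 5 minutes. The extremes are 20 − 20 = 0 and 25 − 15 = 10 minutes.

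**3. Numbers available (To Whom; What (Materials)).**

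- Finland: 200 to 400 by open call plus about 50 from nursing homes = 250 to 450.
- Spain: 20 to 40. All extended-track recruits: 270 to 490.
- Extended-track armband wearers: about 40 in Finland plus 20 to 40 in Spain = 60 to 80.

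Finland is the safer base. The hand dynamometer, body composition analyser and peak flow meter are listed under Finland's equipment only, and Spain may use a modified track.

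**4. Precision.** For the share of variance explained, an approximate 95% half-width is 1.96 × √(4R²(1 − R²)²/n). At an assumed R² = 0.5 this becomes 1.96 × √(0.5/n):

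| n | Half-width |
|---|---|
| 250 | 1.96 × 0.0447 = 0.088 |
| 450 | 1.96 × 0.0333 = 0.065 |
| 60 (wearers) | 1.96 × 0.0913 = 0.179 |
| 80 (wearers) | 1.96 × 0.0791 = 0.155 |

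These are best cases, because participants may skip stations (Tailoring) and the first station is either a 6-minute walk or a nonexercise test.

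**5. What 1 − R² can show.** Unexplained variance includes measurement error. As an assumed illustration, take a station with reliability 0.6 whose true score is fully predicted by the other stations. R² cannot exceed 0.6, so 1 − R² = 0.4 with no new information at all. A narrow interval on R² therefore does not by itself separate redundancy from new information.

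**The case against.** The strongest reply is that this is a condensed article, the sentence sits in the Discussion as an expectation, and regressions among fitness stations are the kind of detail left to a fuller document. The stated aim is to develop and test a protocol in real-life settings; proof of incremental information is not a listed objective. Better understanding can also fairly be read as breadth, and breadth is guaranteed because the comparator is described as less comprehensive.

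Much of this stands. The absence of a regression plan would not be a finding on its own. Breadth does hold by construction. What remains is that the article itself names the comparison and draws a *therefore* that the comparison cannot carry.

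Three stronger readings are tempting, and the documents do not support them:

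- **That the longer track will be recommended whatever the data show.** The text sets no such rule. The recommendation is worded as an expectation and depends on the UX result.
- **That the extended battery's information is never looked at.** Its results will be combined with sensor data. What is missing is any examination of the gain over the shorter protocol.
- **That the added stations are redundant, or that the existing data would settle it cleanly.** The article does not list the manual's stations, so overlap cannot be counted from it. The limits of 1 − R² and the reduced usable numbers also apply.

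**Conclusion.** The point holds as a minor one. UX is the only planned comparison between the protocols, and the expected recommendation also rests on an informational gain that is assumed. The consequence is confined to what case study 4 may conclude about its testing protocol. Its UX comparison and its before-and-after training comparison are unaffected.

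The cost of being wrong is about 5 minutes of track time per person (0 to 10), plus staff effort, in future users of the longer track.

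The verdict assumes that the article's account of the between-protocol comparison is complete as to its subject, which two separate sections support. The feasibility figures assume that recruitment reaches the stated estimates and that most participants complete most stations.

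**What to change.** Either of two changes is enough.

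1. **Limit the conclusion.** In Discussion, Case Study 4, confine the expected conclusion to the user experience and acceptability of the longer track, and delete the statement that it should be applied. This costs one sentence.

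2. **Keep the recommendation, but make it conditional.** State an analysis within extended-track participants, mainly Finland (about 250 to 450 recruited, fewer where stations are skipped):
   - Use the cited manual to split the 12 stations into shared and added.
   - Test whether the added stations, beyond the shared stations plus age and sex, improve explanation of the quality of life score or change participants' classification against the reference values.
   - Report 1 − R² for each added station as descriptive only, because it includes measurement error.
   - Treat armband analyses as exploratory: about 60 to 80 wearers, 24 hours in Finland v 96 hours in Spain, with Spanish wear during the training period.
   - Keep UX as the second condition. If the split leaves too few shared stations to be useful, fall back on option 1.

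Option 2 costs a few regressions on data already to be collected, with no new participants, visits or tests. The recommendation may narrow to a subset of the added stations.
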